### Outcome measures

The primary clinical outcome measure is the difference in the mean total Unified Parkinson’s Disease Rating Scale (UPDRS) scores between the early- and delayed-start groups at 80 weeks (Table 2) [8]. Secondary endpoints are (a) progression of symptoms between Visit 2 and Visit 4 (phase 1) and between Visit 5 and Visit 8 (phase 2) measured with the UPDRS; (b) disability measured with the AMC Linear Disability Score (ALDS), defined as the between-group difference at 80 weeks (Table 2) [9]; (c) between-group difference in mean total UPDRS scores at 80 weeks and the progression of UPDRS scores during phases 1 and 2 in patients who followed the study ‘per protocol’; (d) between-group difference in mean total UPDRS scores at 80 weeks and the progression of UPDRS scores during phases 1 and 2 in patients with UPDRS scores in the highest quartile of scores at baseline who followed the study ‘per protocol’; (e) number of patients that need additional medication during phases 1 and 2; (f) cognitive impairment, measured with the MMSE (Table 2) [10]; (g) depression, measured with the BDI-II (Table 2) [11]; (h) perceived quality of life measured with the Parkinson’s Disease Questionnaire-39 (PDQ-39) (Table 2) [12]; (i) quality adjusted life years (QALY), after applying existing scoring algorithms to derive health utilities from observed European Quality of Life-5 Dimensions (EQ-5D) data (Table 2) [13]; (j) working status and absence from paid work measured with a standardised questionnaire; (k) caregiver burden with a standardised questionnaire; (l) resource utilisation outside of the participating hospitals measured with a standardised questionnaire (for (j), (k) and (l) we used an adjusted version of the Short Form - Health and Labour Questionnaire [14, 15] and iMTA Valuation of Informal Care Questionnaire targeted at the study population [16]); (m) costs per unit decrease of the UPDRS and costs per QALY [17, 18]; (n) number of patients withdrawn from the study or lost to follow up; (o) dyskinesias, measured with items 32 to 35 of the UPDRS part IV; (p) levodopa-induced motor response fluctuations throughout the course of the study measured with items 36 to 39 of the UPDRS part IV and three standardised questions concerning wearing-off phenomena (q) (serious) adverse events defined as the frequency, severity, nature, and duration of any adverse event throughout the course of the study.

**Table 2 Tab2:** Clinical rating scales

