As pointed out earlier, the main outcome in this study will be the comparison between treatment arms on UPDRS scores after the total study period of 80 weeks, since this outcome relates to clinical practice. A difference of four points on the total UPDRS is considered to be clinically relevant [20]. The comparisons of slopes in the secondary analyses serve only to differentiate between the different types of treatment effects (direct symptomatic vs disease modifying). Here we pre-specify the possible inference made on these secondary analyses:if a faster progression is found in the placebo group during phase 1 and the non-inferiority assumption assuming equal progression is met in phase 2, this will be indicative of a true disease-modifying effect;if a faster progression is found in the placebo group during phase 1, but non-inferiority of slopes during phase 2 is not demonstrated, then the results are indicative of only direct symptomatic effects.

With regard to the comparisons of the other secondary outcomes (disability, number of patients that need additional medication for PD, cognitive impairment, mood, quality of life, ability to (maintain) work, use of (informal) care, caregiver burden, levodopa-induced response fluctuations, and side effects), we will use the appropriate parametric and nonparametric statistics. Cost-effectiveness and cost-utility analyses will be performed from a societal perspective with the costs per unit decrease on the UPDRS respectively, the costs per QALY as outcomes. In all analyses statistical uncertainties will be expressed in 95 % confidence intervals.

Subgroup analyses by type of hospital (university medical centre versus non-university medical centre), age and disease duration will be performed. Finally, two additional ‘per protocol’ analyses will be carried, focusing on (a) between-group difference in UPDRS scores at 80 week and the progression of UPDRS scores during phases 1 and 2, and (b) between-group difference in UPDRS scores at 80 weeks and the progression of UPDRS scores during phases 1 and 2 in patients in the highest quartile of scores at baseline. Patients will be excluded from the per protocol analysis if they needed additional PD-medication during the study, if they did not use the correct dose and type of medication (e.g., extended release levodopa formulations), or if they missed either Visits 1, 2, 4, 5 or 8.

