Third, the placebo-controlled phase of 40 weeks was chosen based on the results of the ELLDOPA study, which suggested a possible disease modifying beneficial effect of levodopa evident after 40 weeks of treatment [3]. Ideally, the placebo-controlled phase of 40 weeks would even be longer because if a disease modifying effect of levodopa exists, there would then be more time for the slopes of the two treatment groups to diverge further (Fig. 2). However, because of symptom progression, a placebo-controlled phase of more than 40 weeks would result in the retention of progressively fewer patients in the placebo-controlled phase of the study, making the placebo-controlled phase only slightly longer because of the increasing lower numbers in the delayed-start group – thereby diminishing the theoretical advantage of a longer placebo-controlled phase. More importantly, poorer retention in the delayed-start group would compromise the ability to show a difference between the two groups and would potentially select out patients with a milder or more slowly progressive disease course, thereby diminishing a possible existing difference between the two groups. Also, a longer placebo-controlled phase would result in higher costs in this investigator-initiated study. A study design with an additional delayed-stop (at 40 weeks) arm was rejected because this would require patients that typically need antiparkinson medication at this point would experience increased disability and discomfort due to having treatment withheld.

Fourth, we chose a daily levodopa/carbidopa dose of 300/75 mg. In the ELLDOPA study, three levodopa/carbidopa doses (150/37.5 mg, 300/75 mg or 600/150 mg daily) were tested and compared with placebo for 40 weeks, followed by a two-week washout period. The results suggested a beneficial disease modifying effect of levodopa in all treatment groups, thereby making a strong case to choose the 150/37.5 mg daily dose for the current study. However, in the 150/37.5 mg group, there was also a higher dropout rate [3]. We considered a daily treatment of levodopa/carbidopa 600/150 mg too high because of the risk of more side effects [24] and because in daily practice, starting-doses of levodopa are usually lower.

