All possible outcomes of the LEAP-study are likely to have clinical implications. If the LEAP-study demonstrates a beneficial disease modifying effect of the early initiation of levodopa (Fig. 2), an argument can be made for starting treatment as soon as the diagnosis of PD is made. Subsequently, functional health and quality of life may improve substantially – thereby prolonging the period of higher social functioning and participation in the workforce. If the study indicates that there is no disease modifying effect of levodopa, it can still be argued that there is also no reason to delay the use of levodopa early in the disease: after all, levodopa has a large symptomatic effect. Important to note here is that motor complications seem to relate more to disease severity and disease duration than treatment duration [25]. The third possible outcome is that the LEAP-study shows a negative disease modifying effect after 40 weeks of follow-up. Of course, this would be a strong argument in favour of levodopa sparing strategies.

The reason to perform two subgroup analyses – the per protocol analysis and the per protocol analysis for the patients with the highest quartile UPDRS-scores at baseline – is to address the possibility that a direct symptomatic effect of levodopa would mask a disease modifying effect in this cohort with relatively mild Parkinson’s disease.

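### The per-protocol analyses drop patients who needed additional PD-medication, so they are open to selection bias, probably against early start, and the highest-baseline-quartile question is asked only in that selected set

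*Protocol article*

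**What the plan says.** Outcome measures, item (c), lists as a secondary endpoint the week-80 UPDRS comparison, together with progression in each phase, among those who kept to the protocol. Item (d) asks the same question "in patients with UPDRS scores in the highest quartile of scores at baseline who followed the study", so again only within the per-protocol set. The Statistics section then fixes who leaves that set. The first criterion is a need for more treatment: "Patients will be excluded from the per protocol analysis if they needed additional PD-medication during the study". The second is incorrect use, so a patient also leaves "if they did not use the correct dose and type of medication". The third is attendance: "or if they missed either Visits 1, 2, 4, 5 or 8". Missing Visit 3, 6 or 7 does not exclude.

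The same section makes the primary week-80 comparison intention-to-treat, and analyses the slopes both by intention-to-treat and per protocol. The Discussion gives the purpose of the two per-protocol analyses, which "is to address the possibility that a direct symptomatic effect of levodopa would mask a disease modifying effect". It refers there to the relative mildness of the cohort. In explaining why the placebo phase is not longer than 40 weeks, the Discussion also says that poorer retention in the delayed-start group "would potentially select out patients with a milder or more slowly progressive disease course", and that this would shrink any real difference.

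**The concern.** Needing additional PD-medication is not a baseline characteristic. It is decided during follow-up, largely by how severe the symptoms are, and for 40 weeks only one arm has the symptomatic benefit of levodopa. If more delayed-start patients cross that line, deleting them leaves a delayed-start group that is milder than the one randomised. Its week-80 mean then falls towards that of the early-start group. This is the type of selection that the Discussion itself says diminishes a difference, and here the analysis rule creates it.

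At stake is the reading of endpoints (c) and (d) and of the per-protocol slopes. They are meant to reveal a disease-modifying effect that might otherwise be hidden, yet they may hide part of it. The exposure is greatest in (d): patients with the highest baseline scores are the most likely to need more medication, and no planned analysis asks the high-baseline question in all randomised patients.

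**Working it through.** **1. The plan's own figure.** Inputs from the Statistics section: difference 4, SD 13, two-sided 0.05, power 80%. The normal approximation gives n = 2 × (1.960 + 0.842)² × 13² / 4² = 165.8, so 166 per arm. The exact t-test needs 166.8, so 167 (power 0.8005). Then 167 / 0.75 = 222.7, so 223 per arm and 446 in total. The figures reproduce, so SD 13 and a 4-point difference serve as the yardstick.

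**2. What the documents do not give.** They state a total withdrawal rate of 25%, but no rate of additional medication, no exclusion rate by arm, and no size for the symptomatic effect assumed at the trigger. These are assumptions below. It is also assumed that a phase 1 patient moved early to the week 41-42 capsules counts as having needed additional PD-medication. The Study procedures text describes that switch as a response to needing additional treatment, but the exclusion rule does not say so outright.

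**3. Closed-form check.** Suppose the fraction f with the greatest need is removed from an arm, and need has correlation ρ with the week-80 score. The arm mean moves by −13 × ρ × φ(c) / (1 − f), with c = Φ⁻¹(1 − f).

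For ρ = 0.5:
- delayed, f = 0.25: c = 0.674, φ(c) = 0.318, shift = −13 × 0.5 × 0.318 / 0.75 = −2.75
- early, f = 0.10: c = 1.282, φ(c) = 0.175, shift = −13 × 0.5 × 0.175 / 0.90 = −1.27
- change in delayed minus early: −2.75 + 1.27 = −1.49 (from unrounded values), so a true 4 appears as 2.51

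| Excluded, early / delayed | ρ = 0.3 | ρ = 0.5 | ρ = 0.7 |
|---|---|---|---|
| 10% / 25% | −0.9 | −1.5 | −2.1 |
| 20% / 40% | −1.2 | −1.9 | −2.7 |
| equal fractions | 0 | 0 | 0 |
| 25% / 10% | +0.9 | +1.5 | +2.1 |

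The sign depends on which arm loses more, and the shift is zero if ρ = 0.

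**4. Simulation with exclusion driven by current severity.** Here the arm imbalance arises from the placebo phase instead of being imposed. The week-80 SD is held near 13. For example, intercept SD 11, slope SD 0.06 per week and residual SD 5 give √(121 + (80 × 0.06)² + 25) = √169.04 = 13.0. About 10-28% of delayed and 4-17% of early patients are excluded when the true difference is 4. Results, delayed minus early:

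| | Truth 4, unadjusted | Truth 4, baseline-adjusted | Truth 0, unadjusted | Truth 0, baseline-adjusted |
|---|---|---|---|---|
| Whole per-protocol set | 2.0 to 2.9 | 3.4 to 3.7 | −0.3 to −1.1 | −0.1 to −0.3 |
| Per-protocol top quartile | 1.6 to 2.6 | 2.2 to 3.0 | – | – |

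The all-randomised top quartile returns about 4 when the truth is 4.

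A variant with a hard severity threshold and heavier exclusion (15-44% delayed, 7-28% early) gave 0.9-2.5 unadjusted for a true 4. The size therefore moves with the assumptions, while the direction did not change under severity-driven exclusion.

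**5. Why adjustment helps less in the top quartile.** Across the whole set, much of the selection acts through baseline severity, which covariance adjustment removes. Within the top quartile the baseline range is narrow, and many more patients are near the trigger: one run excluded 38-62% of them, against 17-32% overall. What is left is selection on progression, which baseline adjustment does not remove.

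**The case against.** Excluding deviators is what a per-protocol analysis conventionally does. These analyses are called additional, the primary week-80 comparison and one version of the slopes use all randomised patients, and item (e) reports the number needing additional medication, so a discrepancy would be visible. The plan's week-80 methods include ANCOVA on baseline UPDRS. If that is also applied per protocol, the whole-set shift is modest: 4 becomes 3.4-3.7. All of this stands, and it is why the point is limited to secondary analyses. It does not answer the top-quartile problem, where the adjusted loss is larger and no all-randomised counterpart is planned.

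Several stronger readings are tempting but not supported:

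- *The rule removes fast progressors mainly from the delayed arm.* This is likely, but no rates by arm are given. If early-start patients left more often, for example for a wrong dose or type, the sign would reverse.
- *Missed visits add to the same bias.* Exclusion applies only "if they missed either Visits 1, 2, 4, 5 or 8", and nothing links those absences to fast progression or to one arm. That criterion costs data that a random effects model could use, and no more can be said.
- *With no true effect, early levodopa would look clearly harmful.* Apparent harm of 0.9-2.4 points arises with intercept SD 12, slope SD 0.15 and residual SD 5, but these imply a week-80 SD of √(144 + 144 + 25) = 17.7, against the plan's 13.
- *The top quartile has only about 20% power.* For 29 per arm, that uses the whole-cohort SD of 13. At the narrower SD of about 9.6 seen within the quartile, it is 34-35%. The 29 also rests on a further 30% exclusion that has no source in the article.
- *The Discussion condemns the per-protocol rule.* Its remark concerns a placebo phase longer than 40 weeks. It shows awareness of the mechanism and says nothing about this rule.

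**Conclusion.** The concern holds in limited form. Endpoints (c) and (d) and the per-protocol slopes select on a post-randomisation event that depends on severity and probably on allocation. The likely direction is against early start, contrary to the stated purpose of these analyses. Under the assumptions above, the whole-set loss from a true 4 points is about 1.1-2.0 unadjusted (4 − 2.9 to 4 − 2.0) and 0.3-0.6 baseline-adjusted (4 − 3.7 to 4 − 3.4). In the top quartile it is about 1.0-1.8 adjusted (4 − 3.0 to 4 − 2.2), which is substantial against a clinically relevant difference of 4.

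These sizes rest on assumed exclusion rates, severity-driven exclusion, an assumed symptomatic effect, and the early switch counting as additional medication. A reader might infer that the trial's main conclusion is biased. It is not, because the primary week-80 comparison keeps patients as randomised.

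**What to change.** Three changes to the analysis text:

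1. Ask the high-baseline question in all randomised patients, as a treatment-by-baseline-UPDRS interaction, with the top-quartile estimate reported alongside.
2. Keep the two per-protocol analyses, but label them supportive, adjust them for baseline UPDRS, and state the expected direction of selection.
3. Add a mixed-model analysis in which every randomised patient contributes scores up to the start of additional or incorrect PD-medication, later scores are treated as missing, and the missed-visit exclusion is not applied.

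No visits, patients or treatment change. The cost is a little more analysis work. The added analysis assumes data are missing at random after deviation, given the scores already observed, and it answers a somewhat different question from the conventional per-protocol set. It should therefore stand beside that set and not replace it.

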## Discussion

To differentiate between the direct symptomatic effects and possible disease modifying effects of levodopa, we use a randomised delayed-start double-blind placebo-controlled multi-centre trial design [21]. Some of the choices in the study design warrant discussion.

First, we discuss the stratification for type of hospital, age and disease duration. We stratified by type of hospital (university medical centre versus non-university medical centre) because of possible differing patient characteristics. Stratification by age was chosen because of the different rates of disease progression [22] and because younger patients have a higher risk to develop dyskinesias [23]. Furthermore, younger patients are working more often than older patients, which may bias the cost-effectiveness and cost-utility analyses. Stratification by disease duration was chosen because it is more likely that patients with longer disease duration at the time of inclusion will need the addition of symptomatic medication earlier in the course of the study.

The second relevant issue is the approach we chose for patients that need additional treatment during the placebo-controlled phase of the study. If the treating neurologist decides that a patient needs more treatment, the patient will first start with the capsules initially designated for weeks 41 and 42, after which the patient is certain to be taking levodopa/carbidopa – thereby inducing a placebo effect in patients from the early-start group (which are already on levodopa) and an additional direct symptomatic effect of levodopa in patients from the delayed-start group (which were on placebo) [19]. This procedure prevents unblinding.

Third, the placebo-controlled phase of 40 weeks was chosen based on the results of the ELLDOPA study, which suggested a possible disease modifying beneficial effect of levodopa evident after 40 weeks of treatment [3]. Ideally, the placebo-controlled phase of 40 weeks would even be longer because if a disease modifying effect of levodopa exists, there would then be more time for the slopes of the two treatment groups to diverge further (Fig. 2). However, because of symptom progression, a placebo-controlled phase of more than 40 weeks would result in the retention of progressively fewer patients in the placebo-controlled phase of the study, making the placebo-controlled phase only slightly longer because of the increasing lower numbers in the delayed-start group – thereby diminishing the theoretical advantage of a longer placebo-controlled phase. More importantly, poorer retention in the delayed-start group would compromise the ability to show a difference between the two groups and would potentially select out patients with a milder or more slowly progressive disease course, thereby diminishing a possible existing difference between the two groups. Also, a longer placebo-controlled phase would result in higher costs in this investigator-initiated study. A study design with an additional delayed-stop (at 40 weeks) arm was rejected because this would require patients that typically need antiparkinson medication at this point would experience increased disability and discomfort due to having treatment withheld.

Fourth, we chose a daily levodopa/carbidopa dose of 300/75 mg. In the ELLDOPA study, three levodopa/carbidopa doses (150/37.5 mg, 300/75 mg or 600/150 mg daily) were tested and compared with placebo for 40 weeks, followed by a two-week washout period. The results suggested a beneficial disease modifying effect of levodopa in all treatment groups, thereby making a strong case to choose the 150/37.5 mg daily dose for the current study. However, in the 150/37.5 mg group, there was also a higher dropout rate [3]. We considered a daily treatment of levodopa/carbidopa 600/150 mg too high because of the risk of more side effects [24] and because in daily practice, starting-doses of levodopa are usually lower.

All possible outcomes of the LEAP-study are likely to have clinical implications. If the LEAP-study demonstrates a beneficial disease modifying effect of the early initiation of levodopa (Fig. 2), an argument can be made for starting treatment as soon as the diagnosis of PD is made. Subsequently, functional health and quality of life may improve substantially – thereby prolonging the period of higher social functioning and participation in the workforce. If the study indicates that there is no disease modifying effect of levodopa, it can still be argued that there is also no reason to delay the use of levodopa early in the disease: after all, levodopa has a large symptomatic effect. Important to note here is that motor complications seem to relate more to disease severity and disease duration than treatment duration [25]. The third possible outcome is that the LEAP-study shows a negative disease modifying effect after 40 weeks of follow-up. Of course, this would be a strong argument in favour of levodopa sparing strategies.

The reason to perform two subgroup analyses – the per protocol analysis and the per protocol analysis for the patients with the highest quartile UPDRS-scores at baseline – is to address the possibility that a direct symptomatic effect of levodopa would mask a disease modifying effect in this cohort with relatively mild Parkinson’s disease.

Regardless of these possible outcomes of the LEAP-study, no clear statement can yet be made about the effects of early or delayed starting with levodopa beyond the study period. Some long-term effects of levodopa – such as the development of dyskinesias and response fluctuations – may take years to develop, which may offset any initial beneficial effect evident in the early start group, speaking in terms of total quality-adjusted life years and costs. In this light, the results of the open label PD MED study have to be weighed carefully [2]. This study did not show a difference between the PDQ-39 mobility scores of patients who started treatment with levodopa as compared to patients starting with levodopa-sparing therapy (DA or a Monoamine Oxidase-B inhibitor). A high percentage of patients in the levodopa-sparing arm also received levodopa in different dosages at different times during the follow-up – thereby possibly masking a disease modifying effect of levodopa. Interestingly, the group that started with levodopa used a lower levodopa equivalent dose at the end of the study. This could be due to a beneficial disease modifying effect of early levodopa, but could also be an artifact of the formula used to calculate the levodopa equivalent dose.

